## Results

The primary outcome of this study is the assessment of long-term cognition and psychosocial function. Patient mortality will be the study's secondary outcome. Active enrollment will take place until the end of September 2016 and data collection will conclude at the end of September 2017. The analysis and results are expected to be available by March 2018.

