**Results:**

Long-term cognition and psychosocial function will be the primary outcome of this study. Mortality will also be investigated as a secondary outcome. Active enrollment will take place until the end of September 2016 and data collection will conclude at the end of September 2017. The analysis and results are expected to be available by March 2018.

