### Measures

This study aims to test the hypothesis that delirium during mechanical ventilation in the ICU promotes long-term cognitive and psychosocial decline and impacts one’s health-related quality of life when compared with non-delirium patients [8-23]. The data recorded at study enrolment, during their stay in the ICU, and at discharge are shown in Textbox 1.

 Data recorded at the time of patient enrolment in the study, during their stay in the intensive care unit, and at dischargeCollected dataAt enrolmentDemographic dataNameMailing addressContact numberDate of birthAgeIndigenous statusSexDate and time of admission to the intensive care unit (ICU)ICU admission diagnosis—Acute Physiology and Chronic Evaluation (APACHE II)Date and time of first intubationDailyRichmond Assessment Sedation Scale (RASS)Confusion Assessment Method for the ICU (CAM-ICU)At discharge from the ICUDelirium positive or negativeDate and time of discharge from the ICUSurvival status at discharge from the ICUMini-Mental State Examination (MMSE)After discharge from the ICU (episode outcome at 6 and 12 months)Survival statusDependency statusCognitive status

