### Sample Size

The primary outcome of this study is the relative decrement in MMSE at 6 months after discharge from the ICU. We used the most relevant clinical trial employing MMSE to quantify cognitive function of both delirium-positive and delirium-negative patients to estimate the expected outcomes for our patients at 6 months after discharge from the ICU in order to make a sample size calculation. We estimated the clinically important reductions expected in MMSE and calculated that, at a type 1 error rate of 5% (alpha .05), we can find the clinically significant difference of 2 points on the MMSE between groups with 80% power if we include a minimum of 81 patients in each group (delirious and not delirious). To allow for potential dropouts following recruitment, we plan to enroll 200 patients.

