### Statistical Analysis

All statistical analysis will be done using Statistical Package for the Social Sciences (SPSS) Research Engine, Version 22.0 IBM SPSS Statistics (2015). We plan to employ the Student *t* test to compare mean outcomes in each group when assuming a normal underlying distribution can be justified and the Mann-Whitney U test to compare medians when this assumption fails. We will compare differences in proportionate outcomes using a Chi-square analysis. When calculating multiple time points for the purpose of comparing groups over time, we will apply appropriate correction for multiple testing using the Bonferroni correction. For all of these methods, we will determine if there is a statistically significant difference between the groups (*P* values less than .05). Results will be presented as differences between groups with 95% confidence intervals. We will also consider both analysis of covariance (parametric) or Kruskal-Wallis (non-parametric) testing as appropriate and will investigate the influence of potential confounders and correlations by logistic or multiple regression techniques. Further, we will randomly select two groups of patients (30 delirium-positive and 30 delirium-negative) to cross validate our results and assess whether they are stable for both samples.

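### The primary outcome is defined in two incompatible ways, and whether alpha .05 and 80% power hold depends on which one is kept

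*Protocol article*

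**What the plan says.** The protocol article defines its primary outcome in three places, in two different ways.

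- Sample Size: "The primary outcome of this study is the relative decrement in MMSE at 6 months after discharge from the ICU". This is one cognitive score at one time.
- Results: "The primary outcome of this study is the assessment of long-term cognition and psychosocial function". The results paragraph of the Abstract agrees: "Long-term cognition and psychosocial function will be the primary outcome of this study". Neither gives an instrument or a time. Both list mortality, and nothing else, as secondary.

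The schedule (Abstract, Procedure and Enrolment, Textbox 1) places the MMSE at ICU discharge only. TICS and IES-R are given at 6 and 12 months, and IQCODE goes to the informant once, at 12 months.

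The sample size rests on a single comparison at alpha .05, seeking a "clinically significant difference of 2 points on the MMSE between groups with 80% power", with at least 81 per group and 200 enrolled. No SD is given.

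Statistical Analysis limits the multiplicity rule to comparisons over several time points, where "we will apply appropriate correction for multiple testing using the Bonferroni correction". It continues: "For all of these methods, we will determine if there is a statistically significant difference between the groups", with a threshold of P below .05. It states no rule across instruments.

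The hypothesis in Measures also covers "health-related quality of life when compared with non-delirium patients".

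**The concern.** Both definitions use the words primary outcome, so this is not a matter of abridgement, and no fuller document could make both true. The MMSE does not measure psychosocial function, and the broad version fixes no time. The narrow version cannot be carried out as written either, because no MMSE is scheduled at 6 months.

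With mortality as the only named secondary outcome, TICS, IES-R and IQCODE either all belong to the primary outcome or have no stated rank. An analyst could present any of five between-group comparisons as the main result. In an observational comparison with several scales, a fixed primary outcome is the main protection against choosing the favourable one. The error rate and the power claim both depend on how this is settled.

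**Working it through.** **Step 1: candidate comparisons.** TICS at 6 and 12 months (2), IES-R at 6 and 12 months (2), IQCODE at 12 months (1): 2 + 2 + 1 = 5.

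**Step 2: the plan's own figure.** Inputs from Sample Size: difference 2, alpha .05, power 80%, 81 per group. The SD is missing and sidedness is not stated (two-sided assumed), so 81 cannot be reproduced independently. Solving for the SD by the normal approximation:

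SD = 2 / [(1.960 + 0.842) × √(2/81)] = 2 / (2.802 × 0.1571) ≈ 4.54

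This is a standardised effect of 2/4.54 ≈ 0.44. If the test were one-sided, the implied SD would be 5.12. The sensitivity to the SD (two-sided, alpha .05) is:

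| SD | n per group for 80% | power at 81 per group |
|---|---|---|
| 4.0 | 63 | 89% |
| 4.5 | 80 | 81% |
| 5.0 | 99 | 72% |
| 6.0 | 142 | 56% |

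**Step 3: narrow definition.** One outcome at one time is one test. The time-point Bonferroni rule is not triggered, and alpha .05 with 80% power is internally consistent.

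**Step 4: broad definition, error rate.** Apply the plan's rule as written: TICS and IES-R each split .05 over two times (.025 per test, four tests), and IQCODE is tested once at .05.

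- If independent: 1 − 0.975⁴ × 0.95 = 1 − 0.9037 × 0.95 = 14.1%.
- Upper bound under any dependence: 4 × .025 + .05 = 15%.

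The scores come from the same patients, and TICS and IQCODE both concern cognition. Positive correlation would bring the rate below 14%.

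**Step 5: broad definition, power per test.** If 80% at 81 per group is taken as given, the SD cancels. Power at alpha/k is Φ(2.802 − z), where z is the two-sided critical value at .05/k. This assumes the same standardised effect for every test.

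- k = 2 (alpha .025, z = 2.241): Φ(0.560) = 71%. For 80%: 81 × [(2.241 + 0.842)/2.802]² ≈ 98.1, so 99 per group.
- k = 5 (alpha .01, z = 2.576): Φ(0.226) = 59%. For 80%: 81 × [(2.576 + 0.842)/2.802]² ≈ 120.5, so 121 per group.

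The planned allowance is 1 − 162/200 = 19% loss. At that rate the enrolled totals would be 198/0.81 ≈ 245 and 242/0.81 ≈ 299, against 200 planned.

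**Step 6: quality of life.** The scheduled instruments are MMSE, TICS, IES-R and IQCODE, and Textbox 1 adds survival, dependency and cognitive status after discharge. None is presented as a measure of health-related quality of life. This mismatch has no bearing on alpha or power.

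**The case against.** The strongest reply is that the Sample Size section is the operative definition and the other two statements are loose summaries. The article describes TICS as a telephone-modified MMSE, so the 6-month MMSE outcome may simply mean TICS. On that reading there is one test, no correction is due and 80% stands. The statistical part of this reply is right: a reader might infer that power is necessarily below 80%, and the document does not support that. But the substitution of TICS for MMSE in the primary outcome is not stated, the 2-point difference is given for the MMSE, and the broad definition appears twice.

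A reader might also multiply out five uncorrected tests, 1 − 0.95⁵ = 22.6%, and report about 23% error. That ignores the Bonferroni correction over time that the plan does state; 14% is the figure under the plan's rule. Nor need the P below .05 sentence conflict with Bonferroni, since it can be read as the threshold for corrected P values.

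Finally, the stated aim is exploratory, and correction across non-primary instruments is commonly left to an analysis plan. That is fair for outcomes ranked as secondary. It does not help while the article leaves them unranked or inside the primary outcome.

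**Conclusion.** The contradiction is certain and should be corrected, because the main claim of the study is otherwise undefined. Its numerical consequence is conditional:

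- One outcome at one time: alpha .05 and 80% power are consistent, and there is no error-rate problem.
- Broad outcome under the stated rule: family-wise error up to about 14% if the tests are independent, less if positively correlated.
- Power per test: about 71% with correction for two time points, about 59% for all five tests.

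The power figures take 80% at 81 per group as given (implied SD about 4.5, not stated in the article), a two-sided test, and the MMSE-based standardised effect for every instrument. No effect is stated for TICS, IES-R or IQCODE, so the 59% in particular is illustrative. The quality-of-life mismatch is separate and minor.

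**What to change.** 1. In the Abstract, Sample Size and Results, name the same single primary outcome, one that is actually collected, such as TICS total at 6 months, tested once at two-sided .05.
2. Restate the target difference, SD and sample-size justification on that instrument's scale. The 2 points and 81 per group are stated for the MMSE and cannot simply be carried over.
3. Make 12-month TICS, IES-R and IQCODE secondary alongside mortality. Either apply a multiplicity correction that spans instruments as well as times, or label them exploratory.
4. If both time points stay co-primary, state about 71% power instead of 80%, subject to the re-justification in item 2.
5. Remove health-related quality of life from the hypothesis in Measures.

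These changes should be made and dated before outcomes are compared by group. They need no new patients or assessments. The costs are that psychosocial results become secondary and that the power statement must be justified afresh on the TICS scale, where it may no longer come to 80% with the planned 200 patients.

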## Discussion

The use of sedation and multiple psychoactive medications in the ICU, combined with patients’ metabolic disturbances, underlying infections, and multi-organ failure, may promote delirium and create new or exacerbate existing cognitive impairments [10-23]. Burgeoning evidence has emerged in support of the association between the ICU experience of delirium and adverse patient outcomes, including longer hospital stays and poor functional recovery [40-43]. We hope this study, with its design and comprehensive data collection, will deliver novel insights into the impact of intensive care delirium on patients’ long-term cognitive and psychosocial outcomes, further informing the care of critically ill ICU patients.

## Appendix

Multimedia Appendix 1 Mini-Mental State Examination.

Multimedia Appendix 2 Telephone Interview for Cognitive Status (TICS).

Multimedia Appendix 3 Impact of Events Scale-Revised (IES-R).

Multimedia Appendix 4 Informant Questionnaire on Cognitive Decline in the Elderly (IQCODE).

Multimedia Appendix 5 MMSE:TICS permission.

## Abbreviations

APACHE II: Acute Physiology and Chronic Evaluation
CALD: culturally and linguistically diverse background
CAM-ICU: Confusion Assessment Method for ICU
ICU: intensive care unit
IES-R: Impact of Events Scale Revised
IQCODE: Informant Questionnaire on Cognitive Decline in the Elderly
MMSE: Mini-Mental State Examination
PTSD: post-traumatic stress disorder
TICS: Telephone Interview for Cognitive Status
